## Abstract

**Introduction:**

For the past few decades, condoms have been the main method of HIV prevention. Recent advances in antiretroviral (ARV)-based prevention products have substantially changed the prevention landscape, yet little is known about how popular these products will be among potential users, or whether new methods might be used in conjunction with, or instead of, condoms. This study will use a discrete choice experiment (DCE) to (1) explore potential users' preferences regarding HIV prevention products, (2) quantify the importance of product attributes and (3) predict the uptake of products to inform estimates of their potential impact on the HIV epidemic in South Africa. We consider preferences for oral pre-exposure prophylaxis; a vaginal microbicide gel; a long-acting vaginal ring; a SILCS diaphragm used in concert with gel; and a long-acting ARV-based injectable.

**Methods and analysis:**

This study will gather data from 4 populations: 200 women, 200 men, 200 adolescent girls (aged 16–17 years) and 200 female sex workers. The DCE attributes and design will be developed through a literature review, supplemented by a thematic analysis of qualitative focus group discussions. Extensive piloting will be carried out in each population through semistructured interviews. The final survey will be conducted using computer tablets via a household sample (for women, men and adolescents) and respondent-driven sampling (for female sex workers), and DCE data analysed using a range of multinomial logit models.

**Ethics and dissemination:**

This study has been approved by the University of the Witwatersrand Human Research Ethics Committee and the Research Ethics Committee at the London School of Hygiene and Tropical Medicine. Findings will be presented to international conferences and peer-reviewed journals. Meetings will be held with opinion leaders in South Africa, while results will be disseminated to participants in Ekurhuleni through a public meeting or newsletter.

Strengths and limitations of this studyThis study uses a novel discrete choice experiment (DCE) to elicit people's preferences for new antiretroviral (ARV)-based HIV prevention products.The results of the DCE will allow us to explore how respondents value different product characteristics. We will also be able to predict whether products will be used alongside, or instead of condoms, a critical element of assessing their potential impact.We will draw out policy recommendations from our findings, in particular informing mathematical models to evaluate the impact and cost-effectiveness of a range of new prevention products.The DCE choice tasks are hypothetical in nature and will be carried out in Ekurhuleni Metropolitan Municipality, near Johannesburg, South Africa. The results may not be generalisable to other settings. Female sex workers will be recruited through respondent-driven sampling, rather than a randomised method.

## Introduction

Despite intense efforts to reduce HIV incidence, its estimated prevalence remains high in South Africa. The fourth national population-based survey conducted by the Human Sciences Research Council, estimated prevalence to be 12.6% in 2012, an increase on the previous survey estimate of 10.9% in 2008.^1^ This increase may be explained partly by expanded access to antiretroviral (ARV) treatments and associated reductions in mortality, however, there is also evidence of continued sexual transmission of HIV in those aged 15 years or older. HIV infection is not borne equally in the South African population; women are 1.4 times more likely to be living with HIV compared to men, while adolescent girls (aged 15–19 years) are at 8 times greater risk of being HIV positive than boys of the same age.^1^ Female sex workers (FSWs) are designated a key population for HIV treatment and prevention activities, and are around four times more likely to be living with HIV than South African women of reproductive age from the general population.^2^
^3^

The HIV prevention landscape continues to shift substantially, not least due to emerging evidence that ARV drugs can be used for HIV prevention. The HPTN 052 trial demonstrated the ability of ARVs to reduce the infectiousness of HIV positive persons through suppressing viral loads, and led to the development of treatment-as-prevention programming.^4^ Furthermore, ARV-based oral pre-exposure prophylaxis (PrEP) has been shown to offer a high degree of protection from HIV acquisition in different populations and contexts worldwide.^5–9^ In 2012, WHO recommended oral PrEP for use in specific ‘high-risk’ populations, such as serodiscordant couples. This recommendation was broadened in September 2015 with PrEP recommended for any person at ‘substantial risk’ of HIV acquisition, and not necessarily restricted to those in key populations.^10^

Despite the success and subsequent licensure of oral PrEP, there is an increasing recognition that the characteristics of effective prevention options may vary across different population groups. It is important that prevention options are tailored to fit well with the lifestyles of potential users, and recent efforts have focused on developing novel methods of delivering ARV drugs for HIV prevention. Outside of oral PrEP, there are numerous products in various stages of development including: vaginal microbicide gels used daily or at every sex act; long-acting vaginal rings; a SILCS diaphragm used in concert with gel; and long-acting injectable products.^5^
^6^
^8^
^11–13^

Problems with adherence have plagued clinical trials of shorter-acting products such as microbicide gels, highlighting the need for methods that are attractive and easy for people to use.^6^
^9^ The development of longer acting products, such as the monthly applied vaginal ring or the three-monthly injection, has the potential to increase adherence, uptake and thus effective coverage.^14^
^15^ However, until products have been developed and rolled out to a population, it is difficult to accurately predict whether or how much they will be used, or whether they will be used in addition to, or instead of condoms which offer multipurpose protection.^16^

Attention has also turned to the potential for new products to meet the broader reproductive and sexual health needs of many individuals. These needs are not limited to protection against HIV and other sexually transmitted infections (STIs), but also access to safe and reliable contraceptives. Currently, the only products which protect against HIV, STIs and unwanted pregnancies are the male and female condoms, and so there may be demand for additional product choices which confer combination protection. As such, considerable research has focused on developing multipurpose technologies (MPTs) which offer protection against HIV, STIs and pregnancy.^17^ Efficacy trials for MPTs are planned and products could be made available on the market in the next decade.^11^
^14^

In the context of these advances in the field of HIV prevention, it is important to identify and explore the determinants of demand for new technologies. Understanding user preferences can not only assist prevention efforts by predicting product uptake, but also help refine the development of new products. We plan to undertake a study that will use a discrete choice experiment (DCE) to quantify potential users' stated preferences of ARV-based prevention products in a South African setting, predict uptake of new products, and assess the extent to which condom use might be reduced following their introduction.

DCEs are, theoretically, robust economic tools, and can be particularly informative when there are little or no data on observed behaviour.^18–20^ DCEs ask people to choose between a number of hypothetical scenarios, where each choice is described by a set of attributes. By assessing how choices vary according to different attribute levels, researchers are able to assess what is important to people as they choose. Furthermore, DCEs allow researchers to quantitatively elicit the key drivers of individuals' decisions, and can predict future behaviour.^21^ DCE methods have been used extensively in fields of applied economics, particularly transport and environmental economics.^22–24^ In health, they have been applied across a range of disease prevention areas including voluntary medical male circumcision, vaccination, STI treatment and contraception.^25–28^

A particularly novel use of this research will be for subsequent work to integrate DCE-derived uptake predictions from this study within an infectious disease-modelling framework to estimate the potential impact and cost-effectiveness of introducing new HIV prevention products. Such models often rely on assumed levels of uptake based on expert opinion, or uptake of similar interventions.^29^ These assumptions are frequently not based on data, and so are likely to produce inaccurate projections. This study will build on previous research suggesting that DCEs may provide more data-driven, dynamic and realistic estimates of product uptake in the absence of observed data.^30^

## Methods and analysis

### Overview of approach and methods

This study will build on previous mixed-methods research to explore consumer preferences for HIV prevention products in South Africa. Primary formative research will be carried out among target groups before the implementation of a survey with 800 participants: 200 men and 200 women aged between 18 and 45 years, randomly sampled from the general population, 200 adolescent girls (aged between 16 and 17 years), also randomly sampled from the general population, and 200 FSWs sampled using respondent-driven sampling, a common approach for collecting data from hard-to-reach populations.^31^

The DCE will be carried out among all self-reported HIV-negative persons sampled. Although self-reported HIV status is not necessarily a reliable indicator of serostatus, it can still be useful for hypothetical DCE surveys, assuming that respondents answer according to their perceived HIV status. In an effort to maximise reporting accuracy, we will use an experienced team of interviewers with additional training, focusing on making participants comfortable, and reinforcing confidentiality throughout the interview.

A 2005 study in the same municipality used qualitative focus group discussions (FGDs) and individual interviews to develop a DCE on a set of HIV prevention products under development at the time.^29^ The research identified which product characteristics (or attributes) consumers valued, how the levels of these might vary, and optimal ways to present these to participants in a choice experiment. To develop relevant and meaningful choice tasks, the current study will build on this previous formative research, alongside an updated review of the literature, and intensive piloting with each population.

In a DCE, respondents are presented with a number of options which are each described by attributes of particular levels. Respondents are first asked to choose their most favoured option from two or more alternatives, and then they continue with this process which is repeated over a number of different choice sets. Attribute levels are systematically varied between sets according to an experimental design which aims to maximise the statistical efficiency of data collection. For each choice set, it is assumed that respondents choose the scenario which would give them the most benefit, and choices are, therefore, indicative of an underlying utility function. Econometric analysis of DCE data estimates the utility functions of respondents which quantitatively weights the value placed on each attribute. A more detailed analysis is possible through the inclusion of sociodemographic or other information as explanatory variables in these functions.^32^

DCEs give a quantitative indication of the strength of an individual's preference for one attribute (such as efficacy in preventing HIV infection) relative to another (such as frequency of application). Results from DCEs are conducive to directly informing policy by allowing inference of the key drivers of individual behaviour in responding to different policy environments, and enable the simulation of how choices might change under different circumstances. An example of a DCE is shown in figure 1, where figure 1A represents a vaginal ring, and figure 1B and 1C different injectable products. The opt-out alternative in the final column will be presented as what a respondent reported using in their last sexual encounter, that is, the attributes of a condom if the participant used a condom, or the characteristics of using no protection otherwise. This is to allow the estimation of unconditional demand for new products.

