Two hundred FSWs will be recruited through RDS. We will employ peer educators who will first locate sex work ‘hotspots’ in the Vosloorus area, before selecting 7–10 seeds among FSWs operating in different areas such that different social networks are reached (eg, FSWs working in brothels, on the street or in bars or taverns). These women will be invited to participate in the study and given a ZAR 50 (GBP £2.50) voucher as compensation for their time, before receiving three coupons containing the study information to distribute to colleagues. When one of these colleagues attend the study site, both they and their recruiter receive a small incentive in the form of a ZAR 20 (GBP £1) voucher. The amount of compensation was based on similar studies among FSWs in South Africa, and is designed to be high enough to compensate for potential loss of one client during study participation, but not so high as to encourage significant fraudulent enrolment.

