#### Sample size

The DCE literature has not yet reached consensus on the best way to successfully estimate the sample size required in a DCE study to return meaningful, statistically robust parameter estimates. Applying the popular rule of thumb of Johnson and Orme,^41–43^ we estimate that a sample size of 90 should be sufficient to estimate parameters of the DCE structure shown in figure 1. Similarly, the literature suggests that between 20 and 30 observations per choice set can provide precise parameter estimates.^18^
^44^ This indicates that our sample size of 800 will be sufficient to estimate parameters over the entire population, as well as to explore any variations in preferences which might exist between groups.

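### The sample-size statement counts all 800 surveyed, but only self-reported HIV-negative respondents do the choice experiment; the sex-worker group shrinks most and may fall below 90

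*Protocol article*

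**What the plan says.** In the protocol article, the section on the overview of approach and methods places the formative work "before the implementation of a survey with 800 participants: 200 men and 200 women aged between 18 and 45 years", with 200 adolescent girls and 200 female sex workers making up the rest. The next paragraph restricts the experiment: "The DCE will be carried out among all self-reported HIV-negative persons sampled". The same paragraph concedes that self-report is an imperfect guide to serostatus.

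Under Participants and recruitment, participants are asked to report their HIV status. For the household sample, the interviewer lists all women, men and adolescent girls in the house. For sex workers, "Two hundred FSWs will be recruited through RDS" (respondent-driven sampling), by seeds and coupons. Neither description includes a status screen or a rule for replacing people who report being positive.

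The Sample size section says that "we estimate that a sample size of 90 should be sufficient to estimate parameters of the DCE structure shown in figure 1", adds a literature criterion of 20 to 30 observations per choice set, and concludes: "This indicates that our sample size of 800 will be sufficient to estimate parameters over the entire population". The same sentence extends the claim to exploring differences in preference between groups.

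The Introduction gives a national prevalence of 12.6% in 2012 and a women-to-men ratio of 1.4, and says that sex workers "are around four times more likely to be living with HIV than South African women of reproductive age".

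**The concern.** The number used to judge whether the DCE is large enough is the number surveyed, not the number who will do the DCE. The two differ by everyone who reports being HIV positive, and in this setting that is not a trivial share. The loss is also uneven: it is largest among sex workers, the group whose decisions the article says have never been explored in a DCE.

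There is a practical side. As written, the target of 200 per group can mean stopping at 200 interviews or at 200 completed DCEs. Field teams following the two readings would produce different datasets, and a shortfall found after fieldwork is costly to repair. The uptake predictions are meant to feed later impact and cost-effectiveness models, so a thin group would carry its imprecision forward.

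**Working it through.** **The plan's own figure of 90.** In its usual form the rule of thumb is N = 500c/(t × a), with c the largest number of attribute levels, t the tasks per respondent and a the alternatives per task. Table 1 gives c = 7 (frequency of use) or 5 (product). A choice set has 4 alternatives with the opt-out, 3 without. The text does not give t. The value 90 is attainable: 500×7/(13×3) = 89.7, or 500×5/(7×4) = 89.3. It cannot be confirmed without t, which may be in a figure that is not shown. It is taken as stated here.

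**Inputs from the Introduction.** Overall prevalence 12.6%; women 1.4 times men; sex workers about four times women of reproductive age. No prevalence is given for women of reproductive age, for sex workers or for girls aged 16–17.

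**Assumption.** Half of the population are women. Then:

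- Men: 12.6/(0.5×1.4 + 0.5) = 12.6/1.2 = 10.5%
- Women: 1.4 × 10.5 = 14.7%
- Sex workers, ratio read as a risk ratio: 4 × 14.7 = 58.8%

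**Full disclosure, 200 surveyed per group.**

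- Men: 200 × (1 − 0.105) = 179.0
- Women: 200 × (1 − 0.147) = 170.6
- Sex workers: 200 × (1 − 0.588) = 82.4 (81.6 to 84.3 if women are 48% to 55% of the population)
- Girls: 170.6 to 200, assuming prevalence between the women's rate and zero
- Total: 602.6 to 632.0

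**Half of positives report being negative, in every adult group, all girls counted.**

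- Men: 200 × (1 − 0.0525) = 189.5
- Women: 200 × (1 − 0.0735) = 185.3
- Sex workers: 200 × (1 − 0.294) = 141.2
- Girls: 200
- Total: 716.0

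**Sex workers under other readings.** The last column treats recruits as independent.

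| Reading | Reporting positive | DCE respondents of 200 | Chance of fewer than 90 |
|---|---|---|---|
| 4 × 14.7%, full disclosure | 58.8% | 82.4 | 0.85 |
| 4 × 12.6%, full disclosure | 50.4% | 99.2 | 0.08 |
| Odds ratio of 4 on 14.7%, full disclosure | 40.8% | 118.4 | 0.00002 |
| 4 × 14.7%, half of positives disclose | 29.4% | 141.2 | not computed |

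For the odds reading: 4 × 0.147/0.853 = 0.689, and 0.689/1.689 = 0.408.

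**Break-even.** The group drops below 90 when more than 1 − 90/200 = 55% report being positive. Under the risk-ratio reading with full disclosure, that means a prevalence in women above 55/4 = 13.75%. Starting from 58.8%, the count returns to 90 if 1 − 0.55/0.588 = 6.5% of positives report being negative.

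**Weighting.** The data analysis section commits to weighting the respondent-driven sample, which normally costs precision. The documents give no design effect. An effective size of 90 tolerates a design effect of at most 99.2/90 = 1.10, 118.4/90 = 1.32 or 141.2/90 = 1.57. From 82.4, no design effect of 1 or more suffices.

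**The case against.** **A condensed article.** The full protocol may hold quota and replacement rules, and 200 may have been meant as HIV-negative completers throughout. That would resolve the matter, but the point does not rest on missing detail. The article limits the DCE to some of those sampled and then draws its conclusion from all of them.

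**The 90 is not a per-group minimum.** This stands. The article calls 90 sufficient for the DCE structure. A reader might infer that sex workers breach a floor set by the plan, but no such floor is stated. Using 90 as a yardstick for one group is still reasonable: it is the only respondent number that the section derives, differences between groups are claimed to be within reach, and men see a different product set, so pooled size does not establish adequacy within a group. Against that, exploring differences need not mean a separate sex-worker model, and the second criterion could still be met: 82 respondents allow two blocks at 30 observations per choice set (82/30 = 2.7) or four at 20 (82/20 = 4.1). The number of blocks is not given.

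**The documents do not show that the group falls below 90.** This also stands. Only one of the four readings does so. The calculation chains figures with different base populations, and the filter is self-report, so a small amount of under-reporting restores 90. Under-reporting is a weak defence, though, because the article sets out to maximise reporting accuracy.

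**Design effect.** A reader might assume a value such as 2, which turns 82 to 141 into about 41 to 71, and conclude that the group is too small on every reading. No figure in the documents supports 2 or any other value, so only the break-even values above are safe.

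**Conclusion.** Wrong as written: the stated DCE size is not one that the design delivers. That part needs no outside figure; it follows from setting the eligibility sentence beside the sample-size conclusion.

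The size of the gap does rest on assumptions. With an equal sex split and the stated range for girls, about 603 to 632 people do the DCE under full disclosure, and about 716 if half of the positive adults report being negative. For sex workers, roughly 80 to 140 of 200 remain when one assumption is varied at a time. Combining the odds reading with half disclosure would give more, 200 × (1 − 0.204) = 159. A higher base prevalence among women of reproductive age would give fewer, but the documents do not supply one. Falling below 90 is therefore possible, not demonstrated.

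The pooled conclusion survives, since more than 600 respondents is well over six times 90. What needs correcting is the 800 and 200 as DCE denominators, and the between-group sufficiency statement where it covers sex workers.

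**What to change.** Choose one of two routes and state it in both the overview and the sample-size section.

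1. **Redefine the target.** Make 200 per group the number of self-reported HIV-negative DCE completers. Ask status before a person counts toward the quota, and let HIV-positive recruits in the respondent-driven sample still pass on coupons so that referral chains are not cut. The cost is extra screening contacts. For adults in households this is modest under full disclosure: 200/0.895 = 224 men and 200/0.853 = 235 women. For sex workers it depends on the reading, from 200/0.706 = 284 to 200/0.412 = 486 recruits; reaching only 90 on the least favourable of these readings takes 90/0.412 = 219.

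2. **Keep 800 interviews and restate.** Give the expected DCE sample by group as a range, with the assumed prevalence, disclosure and girls' rate beside it. Add a line on precision lost to weighting in the sex-worker sample, and qualify the between-group sufficiency statement for that group. This costs only wording, at the price of a less favourable stated sample.

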**Figure 1 BMJOPEN2015010682F1:**
[figure not shown]
Example of a discrete choice experiment choice task to elicit HIV prevention product preferences from HIV negative women.

The study design is shown in figure 2, and consists of three stages: an extensive formative phase (including generating an initial design, piloting and pretesting of the DCE), implementation of the DCE and data analysis and publication. The DCE design began in July 2015 and piloting in September 2015. Data collection for the final DCE is expected to be carried out between October and December 2015. This study will conform to the best-practice guidelines of the International Society for Pharmacoeconomics and Outcomes Research Guidelines for Good Research Practices for conjoint analysis in health.^33^

